# Pulsed electromagnetic fields for postmenopausal osteoporosis and concomitant lumbar osteoarthritis in southwest China using proximal femur bone mineral density as the primary endpoint: study protocol for a randomized controlled trial

**DOI:** 10.1186/s13063-015-0780-4

**Published:** 2015-06-10

**Keywords:** Menopause, Pulsed electromagnetic fields, Osteoporosis, Osteoarthritis

## Abstract

**Background:**

Osteoporosis (OP) and osteoarthritis (OA) are prevalent skeletal disorders among postmenopausal women. Coexistence is common especially that of postmenopausal osteoporosis (PMO) and lumbar OA. An hypothesis has been raised that OP and OA might share the same pathogenic mechanism, and pulsed electromagnetic fields (PEMFs) were reported to have anti-osteoporosis and anti-osteoarthritis properties, but this suggestion was based primarily on biomarker data. Therefore, whether these two effects could take place simultaneously has not yet been investigated. This randomized controlled trial (RCT) is designed to explore the effect of PEMFs for PMO and concomitant lumbar OA.

**Methods/Design:**

The study will include PMO patients (postmenopausal women; aged between 50 and 70 years; have been postmenopausal for at least 5 years and diagnosed with OP using proximal femur T-score) with concomitant lumbar OA (patients with confounding disorders like diabetes, hypertension, hyperlipidemia, and previous fracture history, *etcetera*, will be excluded) will be randomly assigned to two arms: PEMFs group and sham PEMFs group. There will be 25 participants in each arm (50 in total) and the outcome assessment, including the primary endpoint (proximal femur bone mineral density), will be performed at 5 weeks, 3 months and 6 months after enrollment.

**Discussion:**

PMO and lumbar OA are prominent public health problem, especially for postmenopausal women. We hope this RCT will provide scientific evidence to primary care of the postmenopausal women regarding the use of these nonpharmaceutical, noninvasive modalities, PEMFs, in managing PMO and lumbar OA.

**Trial registration:**

Chinese Clinical Trial Registry: ChiCTR-TRC-14005156 (28 August 2014).

**Electronic supplementary material:**

The online version of this article (doi:10.1186/s13063-015-0780-4) contains supplementary material, which is available to authorized users.

## Background

Osteoporosis (OP) is characterized by low bone mass and microarchitectural deterioration of bony tissue, with a consequent increase in bone fragility and risk of fractures [1]. This systemic skeletal disease is clinically diagnosed by evaluating bone mineral density (BMD) using dual-energy X-ray absorptiometry (DXA) according to the WHO criteria [2]. Another prevalent skeletal disorder among postmenopausal women is osteoarthritis (OA). It involves a series of pathological changes not only in articular cartilage but also the underlying bone [3], which will probably increase average BMD and interfere with the capability of DXA in detecting OP.

In clinical practice, proximal femur and lumbar spine are the two most common sites measured for BMD assessment. For the former, the most vulnerable region to hip OA is the femur head, which is not included in the measurement, so BMD values of proximal femur are believed to be accurate to some extent. The spine is also susceptible to OA, and spinal OA affects almost 80 % of those aged 40 or above [4]. More specifically, since the thoracic segments are “splinting” by the costovertebral joints, and the cervical spine has relatively low need for weight-bearing, the lumbar segments are regarded as the most susceptible region of the spine to OA [5]. So the coexistence of OP and lumbar OA is common and the diagnosis of OP was suggested to be made based on values of hip BMD rather than that of lumbar spine, unless lumbar OA was not present [6, 7].

On the other hand, the relationship between OP and OA is complicated and controversial [8, 9]. One hypothesis is that they might share the same pathogenic mechanism since it was found that excessive bone resorption, a hallmark of OP, also took place in the early stage in the development of OA. This finding and hypothesis are inspiring, since they indicate there might be treatments that could be used to treat OP and OA at the same time [9–12].

Pulsed electromagnetic fields (PEMFs) might be classified as these treatments, because both anti-osteoporosis and anti-osteoarthritis effects have been reported respectively, but primarily with biomarker data [13–24]. No clinical research has ever been conducted to explore the anti-osteoporosis and anti-osteoarthritis effects of PEMFs simultaneously, especially using clinical data. In the clinical setting, the coexistence of postmenopausal osteoporosis (PMO) and lumbar OA is common, and if treatments could be applied to cope with these two problems at the same time, such a treatment would be significant. The primary goal of this randomized controlled trial (RCT) is to explore these two effects by treating PMO (diagnosed by evaluating BMD of proximal femur) with concomitant lumbar OA in southwest China.

## Methods/Design

### Study design

The research will be a prospective parallel, single-blinded (assessor and participants) RCT with a follow-up period of 6 months. After baseline assessment, participants will be randomized into two arms: PEMFs group and sham PEMFs group (Fig. 1). This randomization process will be automatically performed using software and sequential sealed envelopes by an independent statistician once a patient will be considered eligible. The sealed envelopes will be opened for each participants, and the statistician will make a record of the allocation.

**Fig. 1 Fig1:**
[figure not shown]
Trial flow. PEMFs, pulsed electromagnetic fields

Participants will receive PEMFs or sham PEMFs treatment for the first 5 weeks after enrollment. Outcome assessment will be performed at the following time points: 5 weeks, 3 months and 6 months after enrollment (Additional file 1).

This RCT is planned to be single blinded (assessor and patient). Furthermore, statisticians carrying out the statistical analyses will also be blind to group allocation until the analyses are completed.

This protocol conforms to CONSORT guidelines for nonpharmacological studies [25], in accordance with the ethical standards in the 1964 Declaration of Helsinki and was approved by the clinical research and biomedical ethics committee of the West China Hospital, Sichuan University (ethics reference: 2014 (114)). Written and signed informed consent will be obtained from all participants prior to inclusion in the study. This trial has been registered in the Chinese Clinical Trial Registry (No. ChiCTR-TRC-14005156).

### Participants

To be eligible, participants must meet the following criteria: (1) is a postmenopausal woman; (2) aged between 50 and 70 years; (3) has been postmenopausal for at least 5 years and diagnosed with OP (proximal femur T-score equal to or lower than -2.5) [2, 7]. Women with suspected confounding disorders (for example, diabetes mellitus, hypertension, hyperlipidemia, obesity, secondary and idiopathic osteoporosis, fracture history, systemic inflammatory disorders, visual impairment, severe vestibular lesions, cerebellar lesions, peripheral nerve or muscle disease, mental retardation, mental illness, cognitive impairment, obstetrical and gynecological diseases, blood disease, stroke or venous thromboembolic disease, thyroid, parathyroid, adrenal, hepatic and renal disease, malignancy, *etcetera*), who had received anti-osteoporosis treatment within 6 months before inclusion, and those not suitable to be included for any other reason not mentioned above will all be excluded.

Participants fulfilling the above criteria will receive further lateral lumbar spine radiography, and those with concomitant lumbar OA will finally be included. The diagnosis of lumbar OA will be made when there are two or more criteria fulfilled according to Kellgren and Lawrence [26]. Two technicians will independently read the radiographs and in case of discrepancy, a third technician will be consulted to reach consensus. Further exclusion criteria are as follows: (1) secondary OA; (2) congenital spinal diseases; (3) scoliosis; (4) spondylolisthesis - spondylolysis; (5) history of spinal surgery; (6) inflammatory arthropathy; or (7) individuals who have had facet joint injection or any physical therapy (for example, chiropractic, osteopathy or physiotherapy treatment) for back pain in the previous 6 months.

### Interventions

All included participants will receive conventional usual care (600 mg/day calcium and alfacalcidol vitamin D supplement 0.25 μg/bid) throughout the study period. Participants allocated to the PEMFs group will receive additional PEMFs treatment (40 min/treatment, 1 treatment session/day, 6 treatment sessions/week, for a total of 30 times as one course of treatment) for the first 5 weeks after enrollment, while those assigned to the sham PEMFs group will receive sham PEMFs treatment with the same device but no stimulus generated, indistinguishable from the real ones.

The PEMFs treatment will be applied using XT-2000B therapeutic stimulators (Tianjin xtmed, Tianjin, China) to generate time-varying fields consisting of bursts of asymmetric pulses. Each burst should last for 0.2 ms and repeat at a frequency of 8 Hz. The fields will be delivered perpendicular to the lumbar spine and proximal femur of the supine participant and the flux density within a single burst will start with a peak value of 3.82 mT and decrease to 0 mT in 0.2 ms.

All participants will be asked to refrain from seeking any other physiotherapy or medications throughout the study period, especially during the first 5 weeks after enrollment, when PEMFs are proposed to be delivered. Whereas afterwards, during the follow-up phase when all participants are scheduled to receive only usual care, the use of analgesia and non-steroidal anti-inflammatory drugs (NSAIDs) will be permitted for the sake of ethical considerations. However, the use of this sort of medications should not exceed 3 days in each week and should not occur within 48 h of a follow-up visit. Information regarding the types of treatments and corresponding consumptions will be collected at each visit, and comparability between groups will be tested using Mann-Whitney’s *U*-test.

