### Sample size

Because we could not identify data or citations proving references for the minimum clinically significant difference and corresponding standard deviation in proximal femur bone mineral density (BMDF) between the two arms, the “least detectable longitudinal change measured using dual-energy X-ray absorptiometry (DXA), that is, 0.023” was approximately used as the expected absolute intergroup difference and standard deviation [20, 27]. With a type I error probability of 5 % and a 90 % probability of avoiding a type II error, we would require 20 participants in each group. Assuming a loss to follow-up of 20 %, a total sample size of 50 participants (25 participants per group) is needed.

We did additional sample size calculation for pain intensity, the most important secondary endpoint, measured using the Visual Analogue Scale (VAS) on a scale of 0 to 100. With a standard deviation of 32.17 [28], type I error of 5 %, 90 % power, and a 20 % drop-out rate, approximately 25 patients would be needed in each group to show a minimum clinically significant difference, 30-points between groups [29].

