#### Descriptive analyses at baseline

Baseline comparability between groups will be tested using Pearson’s chi-square test or Fisher’s exact test for categorical data, and Mann-Whitney’s *U*-test for continuous data. All baseline measurements will be analyzed.

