#### Health economics evaluation

To determine whether the PEMFs are cost-effective to pay for additional health gain, we will compute mean (and SD) per patient costs and incremental cost-utility ratios using quality-adjusted life-years (QALYs) derived from SF-36 scores with appropriate preference weightings [35, 36].

For all the analyses mentioned above, a two-sided value of *P* <0.05 will be considered statistically significant. All statistical analyses will be carried out using 19.0 SPSS software (SPSS, Chicago, IL).

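### A Mann-Whitney test at P<0.05 with 20 to 25 per arm cannot show that co-treatment is comparable between arms, and post-randomisation analgesic use should be estimated rather than tested for comparability

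*Protocol article*

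**What the plan says.** All statements are in the protocol article.

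- **Interventions.** Participants are asked to avoid other physiotherapy and medication, above all in the first 5 weeks. Analgesics and NSAIDs are permitted in the follow-up phase, but their use "should not exceed 3 days in each week and should not occur within 48 h of a follow-up visit". Then: "Information regarding the types of treatments and corresponding consumptions will be collected at each visit, and comparability between groups will be tested using" a Mann-Whitney U-test.
- **Health economics evaluation** (closing paragraph, applying to all analyses). "a two-sided value of *P* <0.05 will be considered statistically significant".
- **Sample size.** For the primary endpoint, "we would require 20 participants in each group". "Assuming a loss to follow-up of 20" per cent, "a total sample size of 50 participants (25 participants per group) is needed". VAS pain is called the most important secondary endpoint. No relevant imbalance, margin or power is given for the co-treatment test.
- **Primary analysis and Secondary analyses.** The named covariates are age, menopause age, time since menopause, BMI and the baseline value. Secondary outcomes are adjusted for similar factors. Co-treatment is not named.
- **Data analysis.** The per-protocol analysis covers only the primary outcome at 6 months and counts other treatment only in the first 5 weeks. Descriptive statistics are promised for all variables.

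**The concern.** The stated purpose of the test is to judge comparability, but a test of no difference, without a margin or an interval, can only fail to reject. In a trial this small, failing to reject is a likely result even when use differs by a moderate amount.

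The framing also fails in the other direction. Permitted use begins after randomisation and after the treatment course. If PEMFs relieve pain, sham participants may take more analgesics. A significant difference would then be a consequence of treatment and not evidence that the arms were not comparable. More patients would not cure this.

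What is at stake is how the 3- and 6-month pain results are interpreted. Higher use in the sham arm could hide a true pain difference; higher use in the PEMFs arm could imitate one. The Follow-up section assigns these two visits to the search for delayed effects, and they are the visits preceded by permitted use. Neither a named covariate nor the per-protocol rule addresses that use.

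**Working it through.** **1. Inputs.** From the article: two-sided alpha 0.05; 25 per arm randomised; 20 per arm expected after loss; Mann-Whitney U-test. Assumed, because the article gives nothing: the size of the imbalance in consumption and its distribution.

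**2. The plan's own sample size.** The primary endpoint takes both difference and SD as 0.023, a standardised difference of 1.0. The normal formula gives n = 2 × (1.960 + 1.282)² / 1.0² = 21.0, rounded up to 22 per group, close to the stated 20. Then 20 / (1 − 0.20) = 25, as stated. The co-treatment test therefore has between 20 and 25 per arm. The planned size was set for a difference of 1.0 SD on another variable.

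**3. Miss rate, normal data.** The miss rate is the probability that P ≥ 0.05 when a true difference of d SD exists. Simulated Mann-Whitney tests (asymptotic P, 100,000 runs per cell):

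| Assumed difference | 20 per arm | 25 per arm |
|---|---|---|
| 0.3 SD | 85% | 83% |
| 0.5 SD | 68% | 62% |
| 0.8 SD | 33% | 24% |
| 1.0 SD | 15% | 8% |

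As a cross-check, a t-test at 0.5 SD misses 66% (20 per arm) and 59% (25 per arm). The Mann-Whitney test is slightly less efficient on normal data, so the two agree.

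**4. Miss rate, many non-users.** Analgesic use is likely to contain many zeros. Assume users take 1 to 3 days a week with equal probability (50,000 runs per cell):

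| Assumed users, arm A vs arm B | 20 per arm | 25 per arm |
|---|---|---|
| 30% vs 50% | 77% | 73% |
| 20% vs 40% | 74% | 68% |
| 30% vs 60% | 56% | 47% |
| 20% vs 50% | 51% | 42% |

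**5. What an interval would show.** The half-width of a 95% confidence interval for a difference in means, in SD units, is t × √(2/n). With 20 per arm it is 2.024 × √(2/20) = 0.64 SD; with 25 per arm, 2.011 × √(2/25) = 0.57 SD. Even an observed difference of zero would leave differences of more than half an SD in either direction unexcluded. The P value conceals this.

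**6. Room for use to differ.** Taking 6 months as about 26 weeks, the follow-up phase lasts 26 − 5 = 21 weeks. At 3 days a week, the cap allows up to 21 × 3 = 63 days of use per participant. The cap and the 48-hour limit bind both arms alike; they do not make use equal between them.

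**7. Type of data.** The sentence covers both types of treatment and amounts consumed. Types are categorical, so a Mann-Whitney test can apply only to the amounts.

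**The case against.** Several points on the other side are fair.

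- **No misreading is written into the plan.** A reader might infer that a non-significant test will be reported as proof that VAS is unaffected. The article does not say so: no section links the test to VAS, interprets P ≥ 0.05, or makes a decision depend on it. It can only be said that the result could be read that way. That risk remains, because comparability is the stated purpose and non-significance is the only support for it that the test can offer.
- **The miss rate is conditional.** It is tempting to say that a relevant imbalance is missed about two times in three. That holds only at an assumed 0.5 SD; the article defines no relevant imbalance, so the range must be shown.
- **Miss rates do not measure bias in VAS.** This stands. Nothing in the article allows a consumption difference to be converted into VAS points, and the 3-day cap and 48-hour limit would reduce any effect. The figures show only that the test cannot carry the conclusion its label suggests.
- **The size of any imbalance will be visible.** Descriptive statistics are promised for all variables, so a bare P value is not all that will appear. They do not, however, give the uncertainty of the between-group difference.
- **Leaving use out of the ITT model is defensible.** Agreed: use is post-randomisation and may be caused by treatment, so adding it as a covariate would not be a remedy.
- **Details may sit in an unseen analysis plan.** The absence of a VAS sensitivity analysis from a condensed article is not itself an error. The point rests on the test that the article does specify.
- **Baseline tests.** One might extend the argument to the tests in the section on descriptive analyses at baseline ("Baseline comparability between groups will be tested using"). It does not carry over: baseline differences under randomisation arise by chance, whereas follow-up use may be caused by treatment. Whether to test baseline variables is a separate reporting preference.

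**Conclusion.** The point holds within limits. The article specifies a significance test to judge comparability of co-treatment, and at this sample size a non-significant result cannot establish it. The miss rate is about 62 to 68% at an assumed 0.5 SD imbalance, and between about 85% (0.3 SD, 20 per arm) and 8% (1.0 SD, 25 per arm) over the range examined. The imbalances and the shape of the consumption data are assumptions. The second part needs no arithmetic: because use may respond to treatment, comparability testing is the wrong frame at any sample size.

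The reach is the 3- and 6-month pain results. Permitted analgesic use starts only after week 5, so the end-of-treatment VAS is largely outside the concern. A reader might suspect that the primary bone density endpoint is compromised; nothing in the article supports that, and it is not claimed. The change is worth making because it corrects a stated method cheaply, not because a bias in VAS has been shown.

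**What to change.** In the Interventions section, replace the comparability test with estimation:

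- Report the between-group difference in analgesic/NSAID days and in the proportion of users, each with a 95% confidence interval, for week 5 to month 3 and for month 3 to month 6.
- Present these as a post-randomisation outcome that treatment may influence, and state that P ≥ 0.05 will not be read as comparability.
- Keep the ITT analysis of VAS as planned. Add one prespecified sensitivity analysis of VAS at 3 and 6 months that takes recorded use into account, for example a rank-based composite in which higher VAS and more analgesic days both rank worse.

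The cost is a change of wording and one further analysis of information already due to be collected at each visit. Treatment, visits and sample size are unchanged. The downside is one more sensitivity result and wide intervals, which state openly how little 20 to 25 patients per arm can say about equality of use.

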### Sample size

Because we could not identify data or citations proving references for the minimum clinically significant difference and corresponding standard deviation in proximal femur bone mineral density (BMDF) between the two arms, the “least detectable longitudinal change measured using dual-energy X-ray absorptiometry (DXA), that is, 0.023” was approximately used as the expected absolute intergroup difference and standard deviation [20, 27]. With a type I error probability of 5 % and a 90 % probability of avoiding a type II error, we would require 20 participants in each group. Assuming a loss to follow-up of 20 %, a total sample size of 50 participants (25 participants per group) is needed.

We did additional sample size calculation for pain intensity, the most important secondary endpoint, measured using the Visual Analogue Scale (VAS) on a scale of 0 to 100. With a standard deviation of 32.17 [28], type I error of 5 %, 90 % power, and a 20 % drop-out rate, approximately 25 patients would be needed in each group to show a minimum clinically significant difference, 30-points between groups [29].

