### Assessment

The primary outcome will be the mean percentage change in BMDF at 6-month follow-up. Proposed secondary outcomes were listed below: VAS; The mean percentage changes in bone mineral density of the lumbar spine (BMDL); serum 25-hydroxy-vitamin D (25(OH) D) concentrations; Oswestry Disability Index (ODI); manual muscle test (MMT) score; Berg Balance Scale (BBS) score; Timed Up and Go Test (TUG); hemorheological determinants; serum C-terminal telopeptide of type I collagen (sCTX I), serum bone alkalin phosphatase (sBALP), N-MID osteocalcin (N-MID); range of motion (ROM) of lumbar spine; overall functional ability using short form 36 item general health questionnaire (SF-36, Quality Metric, Inc., Lincoln, Rhode Island, USA); treatment compliance; health care consumption costs; possible adverse events (Additional file 1). Detailed information on some of the outcome measurements are described below:

As for BMD measurements, participants will be scanned in the standard manner by a technician using DXA (GE Lunar iDXA with encore 12.0 software, GE Healthcare Lunar, Madison, WI) following recommendations from the manufacturer. For proximal femur, BMD of the total hip will be recorded and analyzed, while for the lumbar spine the average BMD (aBMD) of the four vertebrae (L1-L4) will be extracted. All these data could be directly obtained using corresponding software without further calculations.

Manual muscle strength of the lumbar and the lower-extremity will be estimated by employing the MMT method with the traditional six-point ordinal Medical Research Council scale (0 to 5). Half-point scores will be used between all grades except that of 4 and 5, since it requires manual resistance that cannot be graded reliably [30]. All tests will be performed by a single examiner. Furthermore, before testing, the examiner and participants will all be required to rest for at least 5 min.

The BBS is a set that comprises 14 simple balance related tasks, ranging from standing up from a sitting position, to standing on one foot [31]. Another examiner will perform the tests for all the participants following the standard procedure. The examiner and participants will also be required to rest for at least 5 min before testing.

A TUG test will be conducted by recording the total time that a person takes to rise from a chair, walk 3 meters, turn around, walk back to the chair, and sit down [32]. It is intended to evaluate the functional mobility of the participants.

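### The stated 90% power with 20 per group is slightly too high for a two-sided 5% test, and it holds only for an assumed 1 SD effect, a condition the protocol does not state

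*Protocol article*

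**What the plan says.** The Sample size section explains that no reference was found for the minimum clinically significant difference in proximal femur BMD (BMDF) or for its standard deviation. It therefore takes the "least detectable longitudinal change measured using dual-energy X-ray absorptiometry (DXA), that is, 0.023", which "was approximately used as the expected absolute intergroup difference and standard deviation". With 5% type I error and "a 90 % probability of avoiding a type II error", it concludes that "we would require 20 participants in each group", and raises this to 25 per group for 20% loss to follow-up. The section does not say whether the 5% is one-sided or two-sided. The level for all analyses is given at the end of the Health economics evaluation section: "a two-sided value of *P* <0.05 will be considered statistically significant".

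Three other places bear on the point. The Assessment section defines the endpoint: "The primary outcome will be the mean percentage change in BMDF at 6-month follow-up". The Primary analysis section compares the groups with a mixed linear model adjusted for age, menopause age, time since menopause, BMI and the baseline value; independent t-tests are a sensitivity analysis. The Data analysis section keeps everyone with a baseline and at least one later value, using last observation carried forward (LOCF).

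**The concern.** Two things do not fit. First, a two-sided comparison at a standardised effect of 1 needs slightly more than 20 per group for 90% power, and a one-sided comparison needs fewer, so the stated 20 follows exactly from neither.

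Second, and more important, a least detectable longitudinal change is a threshold for telling real change in one person from measurement noise. It is not the spread of six-month changes between participants, which is what the SD in a two-group calculation must represent. Entering the same number as difference and SD removes that number from the calculation. The 90% is then a statement about a 1 SD effect, whatever a 1 SD effect turns out to be in BMD units.

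At stake is how the result is read. A null primary result would be set against a 90% claim that reads as power to detect 0.023, although that is so only if the SD happens to be 0.023.

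**Working it through.** **Inputs**
- Difference 0.023 and SD 0.023 (Sample size), so d = 0.023/0.023 = 1.0.
- Type I error 5% (Sample size), two-sided (Health economics evaluation).
- Power 90%, loss 20% (Sample size).
- Two equal arms (25 per group).

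**The plan's own figures**
- Dropout step: 20/(1 − 0.20) = 25 per group. This reproduces.
- Size, two-sided, normal approximation: n = 2(1.960 + 1.282)²/d² = 21.01, rounded up to 22 per group.
- Size, two-sided, t-test (noncentral t): 22.02, rounded up to 23 per group.
- Size, one-sided 5%, normal approximation: 2(1.645 + 1.282)² = 17.13, rounded up to 18; the t-test also gives 18.

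The stated 20 lies between the one-sided and two-sided answers.

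**Power at d = 1, two-sided 5%, unadjusted**

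Normal: Φ(d√(n/2) − 1.960); at n = 20 this is Φ(3.162 − 1.960) = 0.885. The t-test column uses the noncentral t with 2n − 2 degrees of freedom.

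| Analysed per group | Normal | t-test |
|---|---|---|
| 20 | 88.5% | 86.9% |
| 21 | 89.98% | 88.5% |
| 22 | 91.3% | 89.97% |
| 23 | 92.4% | 91.2% |
| 25 | 94.2% | 93.4% |

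At n = 20 the gap to 90% is 1.5 points (normal) or 3.1 points (t-test). For comparison, one-sided power at n = 20 is 93.5% (normal) or 92.8% (t-test).

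**Dependence on the SD**

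Because d = 0.023/0.023, the value 0.023 has no influence on n. If the difference stays at 0.023 and the SD is something else, d changes. Two-sided t-test, 20 per group; every SD other than 0.023 is an assumption, since the protocol gives none:

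| SD of change | d | Power |
|---|---|---|
| 0.018 | 1.28 | 98% |
| 0.020 | 1.15 | 94% |
| 0.023 | 1.00 | 87% |
| 0.025 | 0.92 | 81% |
| 0.030 | 0.77 | 66% |

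**Scale**

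The planning difference is absolute and the endpoint is a percentage change. If difference and SD are rescaled by the same factor, d stays at 1, so n and power do not move.

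**The case against.** The case for leaving the text alone has several parts.

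- **The gap is near rounding.** At 21 per group (normal) or 22 (t-test), power is already within a few hundredths of a point of 90%. This stands: it is a small misstatement, and calling it a clear arithmetic error would go too far.
- **The primary analysis is not an unadjusted t-test.** Covariate adjustment reduces residual variance. With the normal formula, 21.01 × (1 − r²) = 20 gives r of about 0.22; with the t-test, r of about 0.31 is enough (ignoring the few degrees of freedom spent on covariates). These correlations are assumptions. This stands as a possible offset, but the Sample size section neither invokes it nor gives a correlation.
- **LOCF may keep more than 20 per arm.** If all 25 were analysed, power at 1 SD would be 93.4% to 94.2%. A reader might infer from 22/0.8 = 27.5 or 23/0.8 = 28.75 that 28 or 29 must be enrolled per arm. The documents do not support that, because a participant lost after one post-baseline visit remains in the analysis. Equally, the protocol plans on 20, and those without any post-baseline value drop out.
- **The weakness is disclosed.** The Sample size section says that no SD was found and that 0.023 was used approximately, with two cited sources that cannot be checked here; the Discussion calls the calculation somewhat imprecise. A reader might infer a concealed problem with the SD; the text does not bear that out. What the disclosure leaves out is that the 90% is tied to a 1 SD effect and how far power moves with the SD.

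**Conclusion.** The point holds in a limited form. On the protocol's own inputs and its two-sided 5% level, 20 evaluable per group give about 87% (t-test) to 88.5% (normal) power in an unadjusted comparison; the stated 90% needs 22 to 23. That is 1.5 to 3.1 points, or two to three participants per group after rounding up.

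The weightier part is that the power is conditional on a 1 SD effect by construction and is not tied to any documented BMDF difference. Nothing in the protocol supports the stronger reading that the trial is seriously underpowered: the true SD could lie on either side of 0.023, and adjustment or retention could close the small gap. The mismatch between absolute and percentage scales is secondary and changes no number.

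These conclusions assume equal arms, a common SD and, for the headline power, exactly 20 analysed per group without adjustment.

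**What to change.** Keep 25 per arm. In the Sample size section:

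1. State that the calculation is two-sided at 5%.
2. Replace the 90% claim with about 87% power (t-test) for a difference of 1 SD with 20 evaluable per group, before any gain from covariate adjustment or from LOCF keeping more than 20 per arm.
3. Present 0.023 as an assumed SD, and give power in both directions for a difference of 0.023 at n = 20: for example 98% at SD 0.018, 81% at 0.025 and 66% at 0.030, labelled as assumed values.
4. Optionally, express the difference and SD as percentage change to match the endpoint; this leaves n unchanged.

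The cost is a few sentences. No extra participants and no change to the analysis are needed; the stated power becomes slightly less favourable.
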